### Observational study of CST in practice

The design is a multi-centre, longitudinal observational study with people with dementia. Sites that are currently running or in the process of setting up CST groups complete minimal outcome measures at three time points with people with dementia who are participating in the CST and maintenance CST programme (Figure 3). The measures are being completed before the group starts (baseline), 7 or 14 weeks depending on how they implement the CST programme (once or twice weekly), and after the maintenance CST at 31 or 38 weeks. The intervention is CST as routinely offered in the care setting. The aim of this study is to determine whether groups are running in practice and demonstrate the positive findings for cognition and quality of life of life for the person with dementia found in previous CST research [5,11].

**Figure 3 F3:**
[figure not shown]
Flow diagram of observational study and assessment schedule.

### Recruitment

Centres that are running CST groups are approached, and the staff asked to complete measures in cognition and quality of life with the people with dementia taking part in the groups. The centre type, level of staff experience and training are recorded. The centres are given the maintenance CST manual and staff training DVD. Recruited participants have a confirmed diagnosis of mild to moderate dementia.

### Participants

Centres that are currently running or setting up CST groups are approached to participate in the observational study. Approximately 13 centres are needed to provide us with 100 people with dementia and experienced staff in dementia care. The person with dementia will have (1) a score of between 0.5 and 2 on the Clinical Dementia Rating scale [26] and (2) a diagnosis of dementia, (3) adequate spoken and written English, (4) the ability to participate in a ‘meaningful’ conversation and (5) remain in a group for 45 min. Participants also need (6) adequate eyesight and hearing, (7) to be able and willing to give informed consent, and (8) able to complete a cognition and quality of life measure at three intervals over a year. If five to eight people with dementia give informed consent to complete the minimal outcome measures, with a staff member or researcher, the centre is recruited in to the study and a letter explaining their participation in the research is sent to their GP.

### Training package

The staff members within the centres have the CST manual or previously attended CST training, which includes the CST manual. In addition the centre will receive the Maintenance CST manual and DVD.

### Randomisation

This is a naturalistic study of CST in practice so people with dementia who are about to start CST groups are approached and informed, and consent obtained. They are then assessed at three time points (0, 7 and 31 weeks or 0, 14 and 38 weeks) throughout their participation in the trial.

### Outcome measures

The primary and secondary outcome measures for people with dementia are completed at baseline (T0) prior to the CST programme starting, then post CST groups (T1) (at 7 or 14 weeks depending on whether groups are implemented once or twice weekly). The final follow-up will be completed 24 weeks after the maintenance CST has commenced (T2). Socio-demographic information is collected about the person with dementia including age, gender, race, diagnosis of dementia, type of diagnosis and medication. Medication will be recorded at each follow-up to mark any differences for the duration of their participation in the trial.

a) The primary outcome is cognition as measured by the Mini Mental State Examination (MMSE) [27]. The MMSE has a score of up to 30 points and is widely used as a brief indicator of level of cognitive impairment. It has good reliability and validity.

b) The secondary outcome measure is quality of life as measured by the Quality of Life-Alzheimer’s Disease (QoL-AD) [28]. The QoL-AD is a 13-item scale measuring different aspects of life. The scale totals 52 points and higher scores indicate better quality of life. It has good internal consistency, validity and reliability [28,29].

### Consent

It is expected that the participants are competent to provide informed consent to participate in the trial. The British Psychological Society guidance on evaluation of capacity will be adhered to. In addition, consent is an on-going process as opposed to a one-off decision and this will be continually monitored throughout the study. Mental Capacity Act [30] guidance will also be applied where relevant, such as when then a participant is no longer able to give informed consent. A person’s preference can be indicated by their initial willingness to participate in the trial. However, if any distress or discomfort is evident during the study the person will be withdrawn. Ethical approval was granted on June 2011 by East London REC 3.

### Blinding

Blinding is unnecessary for the staff members and researchers, as each person with dementia has the opportunity to participate in the CST and maintenance CST programme and the staff members are completing the assessment at each time point.

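### Observational study: treating everyone with CST does not make masked or consistent outcome assessment unnecessary, and the article differs on who assesses

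*Protocol article*

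**What the plan says.** All references are to the Protocol article, part on the observational study of CST in practice.

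- **Blinding** dismisses the need: "Blinding is unnecessary for the staff members and researchers, as each person with dementia has the opportunity to participate". The same sentence gives a second reason: "the staff members are completing the assessment at each time point".
- **Recruitment** places assessment with the centres that deliver the programme: "Centres that are running CST groups are approached, and the staff asked to complete measures in cognition and quality of life".
- **Participants** describes the arrangement differently. People consent to "complete the minimal outcome measures, with a staff member or researcher".
- **Outcome measures** names MMSE as primary and QoL-AD as secondary, taken before CST (T0), after CST (T1) and at the end of maintenance CST (T2).
- **Analyses** specifies a pre-post comparison in which everyone receives CST and maintenance CST. The covariates are age, gender, cholinesterase inhibitor and the baseline scores, with centre as a random factor. No term refers to the assessor.
- **Introductory paragraph** and **Table 1** give the purpose: to see whether the earlier favourable results on cognition and quality of life appear in practice, and to assess effectiveness there.

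**The concern.** Neither reason in the Blinding section supports its conclusion. That everyone is treated means there is no allocation to hide. It also means that every assessor knows the participant is treated, and that no comparison group carries the same expectation. That staff of the centre do the testing is the source of the risk, not a protection against it.

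Prompting, lenient scoring or a change of tester between baseline and follow-up would look the same as a benefit of CST. The Analyses section expects gradual decline in dementia, so an upward shift could also make decline look like maintenance. These are the readings on which the study's claim about effectiveness in practice would rest.

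Separately, the Blinding and Participants sections do not name the same assessors. A centre cannot tell from the article whether a researcher may test, or whether the type of tester must stay the same for one person.

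**Working it through.** There is no stated figure to reproduce. The article mentions a sample size calculation for the observational study but gives no effect size, SD, significance level or power for it.

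**1. The sections side by side.** Blinding, read alone, means staff at every time point, hence one assessor type. Participants allows staff or a researcher. Read together, they neither require nor rule out a switch within a person. Neither section, nor Recruitment, says whether the assessing staff are those who run the group.

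**2. How an assessor effect enters.** Let δ be the true mean change and a(t) the mean assessor effect at time t. Then

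expected observed change = δ + [a(follow-up) − a(T0)].

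- With a control arm whose assessors did not know the arm, the bracket would appear in both arms and cancel. Here it does not cancel.
- A stable difference between assessor types cancels if the type is constant for each person. Expectation that grows with knowledge of the time point does not cancel.
- Age, gender, drug use and baseline score do not identify the bracket. A random centre effect absorbs differences between centres. It does not absorb a shift common to all of them, or a change of tester within a person.
- If everyone's follow-up score is raised by d points, the error is d. If a net fraction f switches to a tester who scores d points higher, the error is f × d. With an assumed d = 1 MMSE point this runs from 0 (f = 0) through 0.5 (f = 0.5) to 1 (f = 1). Switches that are random in direction have f near 0 and mainly add noise.

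**3. What a given shift would do to the test (illustration only).** Assume no true change, a two-sided 5% one-sample test of mean change, and a systematic shift of b SDs of change. Then

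P(significant improvement) = Φ(b·√n_eff − 1.96), with n_eff = n / [1 + (n/13 − 1)·ICC].

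Inputs: 100 people in about 13 centres (Participants). The less favourable case borrows 15% attrition and ICC 0.05 from the staff trials, neither of which is stated for this study: n = 85, design effect 1 + (85/13 − 1) × 0.05 = 1.277, n_eff = 85/1.277 = 66.6.

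| Assumed shift b | n = 100, ICC 0 | n = 85, ICC 0.05 |
|---|---|---|
| 0 (nominal) | 0.025 | 0.025 |
| 0.1 SD | Φ(1.00 − 1.96) = 0.17 | Φ(0.82 − 1.96) = 0.13 |
| 0.2 SD | Φ(2.00 − 1.96) = 0.52 | Φ(1.63 − 1.96) = 0.37 |
| 0.3 SD | Φ(3.00 − 1.96) = 0.85 | Φ(2.45 − 1.96) = 0.69 |

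The shift that gives an even chance of a spurious positive result is 1.96/√n_eff: 1.96/10 = 0.20 SD and 1.96/8.16 = 0.24 SD. For a fixed shift the probability rises with n_eff, so more participants do not help.

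**The case against.** The best case for the plan is that this is a naturalistic study of CST as centres deliver it, with few measures taken by the sites themselves. With no allocation, blinding in its usual sense has nothing to act on, and staff assessment is openly disclosed. Rules on tester continuity and custody of forms commonly sit in a full protocol that is not shown. Expected decline and retest effects also enter an uncontrolled change, and assessor rules correct neither.

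Much of this stands, and it limits what may be inferred. A reader might conclude any of the following, and the document supports none of them:

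- **That facilitators test their own group members.** Recruitment says only that staff of the centres complete the measures. Overlap is possible but not stated.
- **That testers do switch from researcher to staff.** The wording in Participants sits in a sentence about centre eligibility, and Blinding read alone implies one type throughout.
- **That staff rate the QoL-AD.** Eligibility requires the person with dementia to be able to complete both measures, and Recruitment has staff completing them together with the person. Lenient scoring is therefore not shown for that outcome, although the presence of a familiar tester could still matter.
- **That the bias is half a point, or any other figure.** d, f and b are assumptions.

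The objection does not dispose of the point, because the point does not rest on omitted detail. The article gives a reason that does not support its conclusion, and two of its sections differ. Pragmatism about how CST is delivered does not require leaving outcome measurement uncontrolled.

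**Conclusion.** The point holds in limited form. Declaring blinding unnecessary because everyone is treated is unsound: it confuses blinding to allocation with protection against detection bias. In an uncontrolled before-after analysis a systematic assessor shift passes into the estimated change in MMSE, and possibly QoL-AD, one for one. The article also leaves unsettled who assesses.

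The size is unknown and cannot be derived from the document. The illustration shows only that a shift of about 0.20 to 0.24 SD of change would give an even chance of a false positive. It assumes no true change and a test at the two-sided 5% level, with attrition and ICC either absent or borrowed from the staff trials. It is not evidence that such a shift exists.

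This is a worthwhile, cheap improvement to the observational study. It does not touch the randomised TROU and MONOU comparisons.

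**What to change.** Reconcile the Participants and Blinding sections on who assesses, and replace the statement that blinding is unnecessary with a rule on assessment:

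1. A participant is tested by the same assessor type at T0, T1 and T2.
2. Where another staff member, or the researcher already allowed under Participants, is available, the assessor does not facilitate that participant's group.
3. Earlier score sheets are not available at later tests.
4. Assessor role is recorded at each visit. Sensitivity analyses examine the result by assessor role (facilitator or not) and in participants whose assessor type did not change.

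Add a sentence stating that assessment remains unmasked and that this limits claims of effectiveness. The steps have different reach: the first addresses a switch of assessor type, the second and third reduce expectation, and the fourth makes both visible. Together they reduce expectation bias but do not remove it, since a tester can still know the time point and remember earlier answers.

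The cost is revised wording, one field on the form and some scheduling effort in the centres. Instruments, visits and delivery of CST are unchanged. The article gives its status as ongoing, so assessor role is best recorded from now on, as it may not be recoverable later.

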### Analyses

Analysis will be a pre-post analysis based on intention to treat, in that all collected data made available by the person with dementia will be included, regardless of whether they complete the programme or not. Imputation methods such as the last observation carried forward are of limited use in dementia, as there is the expectation of a gradual decline and for participants to be lost through illness or death. A linear regression model will be used where data are missing in order to predict the missing value and impute the total when possible. The sample size calculation accounts for the number of people expected to be available at the study end point. All participants are in receipt of the CST and maintenance CST programme. Analysis will take into account the evaluation at 24 weeks after CST as the primary end point. Secondary analysis will consider the effects immediately following the CST programme. Age, gender, cholinesterase inhibitor and baseline scores on the two scales being measured will be entered as covariates, together with ‘centre’ entered as a random factor.

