## Methods

### Design

This study includes three projects. The training and outreach trial and the monitoring and outreach trial differ in how staff members are recruited and in their previous exposure to training in CST. The observational study focuses on the effects of CST on people with dementia in the practice context. The three projects together will provide evidence on the most effective way of facilitating the implementation, uptake and effectiveness of the approach in a clinical context (see Table 1).

**Table 1 T1:** Project overview

**Title**	**Training and outreach trial**	**Monitoring and outreach trial**	**Observational study**
**Aim**	To assess the effectiveness of staff training and outreach support	To assess the implementation in practice of CST and outreach support	To assess the effectiveness of CST in practice
**Participants**	Dementia care staff	Dementia care staff	People with dementia
	No previous CST experience or training	Previously received CST manual/training	
**Number**	120	120	100
**Resources**	CST manual maintenance CST manual DVD	CST manual maintenance CST manual DVD	CST manual maintenance CST manual DVD
**Training**	Yes	Variable	Variable
**Outreach**	50%	50%	No
**Assessment timeframe**	Baseline, 6 and 12 months	Baseline, 6 and 12 months	Before and after CST (0, 7 or 0, 14 weeks) and maintenance CST (31 or 38 weeks)

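### The single-arm observational study is asked to show effectiveness, but its planned pre-post change cannot separate a CST effect from decline and other changes over time

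*Protocol article*

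**What the plan says.** The section on the observational study describes one cohort: "The design is a multi-centre, longitudinal observational study with people with dementia". The Analyses section for that study confirms that nobody is untreated: "All participants are in receipt of the CST and maintenance CST programme". It sets the type of analysis, "Analysis will be a pre-post analysis based on intention to treat", and the time point, "Analysis will take into account the evaluation at 24 weeks after CST as the primary end point". The model is described in one sentence: "Age, gender, cholinesterase inhibitor and baseline scores on the two scales being measured will be entered as covariates". That sentence also adds a random effect for centre. It does not say whether the response is the follow-up score, the change score or the repeated scores, or which term will be reported as the change.

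The same section rejects carrying the last observation forward because scores are expected to fall gradually and participants to be lost through illness or death. It gives no rate of decline.

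Table 1 in the Design section states the aim as "To assess the effectiveness of CST in practice". The study's opening section says it should show in practice the positive cognitive and quality-of-life results of earlier CST research, without a figure or a method of comparison. The Discussion says the study evaluates long-term benefits of CST and maintenance CST. Final measures are taken "after the maintenance CST at 31 or 38 weeks".

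**The concern.** An effectiveness claim needs some idea of what would have happened without CST. Here there is no untreated group, no stated rate of decline, no external benchmark and no criterion for success. The one statement about the expected course is that people will get worse. On the plan's own account, then, a test of mean change against zero does not test for an effect. A small fall in MMSE could hide a benefit. A rise could come from repeat testing, from regression to the mean, or from assessment by unblinded staff (the Blinding section for this study says staff complete the assessments). The covariates do not help, because adjusting for age, gender, medication and baseline cannot create a comparison that the design lacks.

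The baseline covariate raises a second, smaller question. Baseline adjustment is usually used to sharpen a comparison between groups. With one group, it has to be clear which term is the mean change and whether its standard error is right.

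**Working it through.** **Sample size.** The 100 participants cannot be reproduced, since no alpha, power, effect, SD or dropout is given for this study. Only the centre arithmetic can be checked: 100/13 = 7.7 per centre, within the required five to eight.

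**What the change measures.** Observed mean change = CST effect + natural course + regression to the mean + repeat testing. Only the left side is observed. Setting the last two terms to zero and assuming a natural decline D over the study:

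| Assumed D (MMSE points) | Effect implied by observed change of 0 | Effect implied by observed change of -1 |
|---|---|---|
| 0 | 0 | -1 |
| 1 | +1 | 0 |
| 2 | +2 | +1 |

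The same result can thus mean harm, nothing or benefit. To compare this with sampling error, assume SD 5 at both visits and correlation r = 0.7. The SD of change is 5 × √(2 × 0.3) = 3.87, the standard error with n = 100 is 0.387 (ignoring centre), and the 95% half-width is 1.96 × 0.387 = 0.76 points. A 1-point uncertainty about decline therefore exceeds the sampling uncertainty, and a larger sample would not reduce it. Regression to the mean cannot be sized: entry is by the Clinical Dementia Rating and ability to take part, not by MMSE.

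**Does the baseline covariate bias mean change?** Not in itself. Simulated data with 13 centres of 8 people (assumed baseline mean 18, SD 4.5; residual SD of change 3; slope of change on baseline -0.2; centre SD 0.7; 600 runs; ordinary least squares) gave:

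| True change | Intercept, covariates centred | Intercept, covariates uncentred |
|---|---|---|
| -2 | -2.00 | 1.5 |
| -1 | -1.00 | 2.7 |
| 0 | 0.00 | 3.5 |
| +1 | +1.00 | 4.7 |

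The adjusted follow-up score at mean baseline minus mean baseline, and the time term in a long-format model, gave the same values as the centred column. The uncentred intercept is the change predicted at age 0 and MMSE 0. With baseline alone, mean 18 and r = 0.7, it is (1 - 0.7) × 18 = 5.4 when nobody has changed on average.

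**Standard error with one group.** With equal SD σ at both visits, the variance of change is 2σ²(1 - r). After adjustment for baseline, the residual variance is σ²(1 - r²). The adjusted standard error treats the sample's mean baseline as fixed, so its ratio to the correct one is √[(1 - r²) / (2(1 - r))] = √[(1 + r)/2]. The false-positive rate of a nominal 5% test is about 2 × [1 - Φ(1.96 × ratio)].

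| r (assumed) | Ratio | False positives |
|---|---|---|
| 0.6 | 0.894 | 8.0% |
| 0.7 | 0.922 | 7.1% |
| 0.8 | 0.949 | 6.3% |

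A simulation of this setting (n = 100, mean 18, SD 5, no true change, no centre effect, 40,000 runs) gave 8.0%, 7.2% and 6.0%. The plain paired change gave about 5% throughout.

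**The case against.** The best defence is that the study is openly labelled observational and naturalistic. It follows controlled trials that already carry the efficacy claim, and it names earlier CST findings as its reference. A condensed article may also leave the choice of response and the coding of covariates to a fuller document. Much of this stands. The design is legitimate for describing routine practice, and silence on centring is not an error. It does not rescue the stated aim: effectiveness and benefits are claimed in the article itself, and the reference to earlier findings comes with no figure and no method of comparison.

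Three stronger readings are tempting and are not supported.

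- A reader might infer that the model has no valid term for the change, or that it will report a spurious gain such as 5.4 points. That follows only if covariates are left uncentred and the intercept is read as the change. The protocol says neither, and the centred model returns the true change.
- A reader might infer that 31-week and 38-week visits are wrongly pooled. Both mark the same point in the programme, since 7 + 24 = 31 and 14 + 24 = 38, and nothing says schedule will be ignored. Elapsed time does differ, so schedule belongs in the model, but this is minor.
- A reader might take the Discussion's phrase about definitive evidence as a claim for this study. It is made for the whole programme.

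**Conclusion.** The concern holds as a mismatch between claim and design. Mean change in MMSE and QoL-AD can be estimated, but it is not a measure of effectiveness, because everyone is treated and decline is expected. The documents give no rate of decline, so the gap cannot be sized from them. Under assumed declines of 0 to 2 MMSE points, the effect implied by a given result shifts by 0 to 2 points.

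The baseline covariate is a secondary matter. It causes no bias when covariates are centred. It does give a standard error that is slightly too small for the population mean change, with about 7% false positives at r = 0.7 and 6% to 8% over r = 0.8 to 0.6, assuming equal SDs at both visits and ignoring clustering by centre. The MMSE means, SDs and correlations used here are all assumptions.

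**What to change.** - **Aim and conclusion.** In Table 1, the study's opening section and the Discussion, restate the purpose as describing change in MMSE and QoL-AD during CST and maintenance CST in routine practice.
- **Estimand and model.** Report mean change from T0 to T2 (primary) and from T0 to T1, with 95% confidence intervals, from a linear mixed model. Take all three visits as responses, visit and schedule (or actual weeks) as fixed effects, and participant and centre as random effects. Age, gender and cholinesterase inhibitor use can stay, centred.
- **Baseline scores.** Leave the baseline outcome score out as a covariate. If it is kept, centre the covariates, use a standard error that allows for the sampling of baseline, and do not read an uncentred intercept as the change.
- **Earlier findings.** Set the result beside earlier CST results only as a descriptive, non-randomised comparison.

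The cost is rewording and some analysis work, with no new data. The downside is a more modest claim.
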